#### Contact coverage (primary outcome)

The contact coverage outcome (PHQ-9 score > 4) will be documented directly through screening in the health centres. After confirming the village of residence of the screened individual, the contact coverage outcome will be allocated to the arm to which their village belongs, regardless of the health centre in which they screen positive.

The contact coverage population level outcome data will be collected through the period of the trial at all thirty health centres, i.e. even at the two health centres which will not be randomised. This is because, while these two health centres do not have discrete village clusters associated with them (as described earlier), individuals with depression from other randomised village clusters could potentially access depression care in these health centres and hence will contribute to the contact coverage outcome.

#### Effectiveness and cost-effectiveness of the integrated intervention

Individual level outcome data will be collected at 3 months and 6 months post-recruitment for those eligible for the effectiveness coverage outcome. The second primary outcome will be mean PHQ-9 score at 3 months post recruitment. The primary endpoint for effectiveness of the integrated intervention is 3 months post recruitment, as we would expect the optimal effect of HAP at that timepoint. The 6-month endpoint is included to evaluate the sustainability of the effect of HAP.

The outcome assessment measures are summarised in Table 2. Depression awareness will be measured using a bespoke tool designed based on the content of the community intervention. The tool will be administered to a consecutive sample of 40 attenders at all the health centres on randomly selected days at baseline and at 6 and 12 months of implementation. Out-of-pocket costs for receiving care, and related non-medical costs, will be collected using a survey tool developed for the purpose which incorporates the Client Service Receipt Inventory (CSRI), a tool that has been used extensively in the study setting [15, 16, 20]. Out-of-pocket costs for receiving HAP intervention (e.g. time loss, travel) will be measured using a survey tool. Standardised disability scores used to estimate quality-adjusted life years (QALYs) will be collected using the WHO Disability Assessment Schedule 2.0 (WHODAS 2.0), which has also been used extensively in this and other settings [16, 21]. The WHODAS assesses behavioural limitations and restrictions related to an individual’s participation, independent from a medical diagnosis [22]. Perceived social support will be measured using a bespoke tool and the Multidimensional Scale of Perceived Social Support (MSPSS) a 12-item instrument designed to measure an individual’s perception of support from family, friends, and a significant other [23]. MSPSS has been widely used and validated in the study setting [24–26]. Additionally, perceived social support related to *Sangathis* will be measured using a bespoke tool. The PREMIUM Abbreviated Activation Scale (PAAS) is a five-item scale, originally developed and used in the trial of the HAP [15, 16] and is based on the Behavioural Activation for Depression Scale (BADS) [27]. It includes five self-reported indicators of behavioural activation such as engagement with a variety of activities and associated pleasure and mastery.

**Table 2 Tab2:** Outcome evaluation

**Outcome**	**Tool**	**Description**	**Population**	**Timeline**
*Primary*				
Contact coverage	PHQ-9	PHQ-9 score > 4 as a proportion of those screened	Adult health centre attenders	Until we achieve target sample size
Effectiveness coverage	PHQ-9	Mean PHQ-9 score	Individuals who consent to receive HAP	3 months post recruitment
*Secondary*				
Sustained effectiveness	PHQ-9	Mean PHQ-9 score	Individuals who receive HAP	6 months post recruitment
Remission	PHQ-9	PHQ-9 score < 10	Individuals who receive HAP	3 and 6 months post recruitment
Response to treatment	PHQ-9	> 50% reduction in PHQ-9 score	Individuals who receive HAP	3 and 6 months post recruitment
Cost-effectiveness	(1) Inventory form for collecting system-level economic costs of delivering interventions (2a) Client Service Receipt Inventory form for collecting costs to patients (2b) Survey form for collecting costs of receiving HAP intervention to patients (3) WHODAS	(1) System-level costs: economic costs in WHO six building blocks for delivering the interventions (2a) Out-of-pocket costs for receiving general medical care and the related non-medical costs (e.g. time loss, travel) (2b) Out-of-pocket costs for receiving HAP intervention (e.g. time loss, travel) (3) Standardised disability scores used to estimate QALYs	(1) Finance records and individuals involved in delivery of the interventions (2a) Individuals who receive HAP (2b) Individuals who receive HAP (3) Individuals who receive HAP	(1) System-level costs: monthly, during the period of implementation (2a) Patient-level costs: 3 and 6 months post recruitment (2b) Patient level costs: 3 months post recruitment (3) 3 and 6 months post recruitment
Depression Awareness Questionnaire	Bespoke tool	Awareness about depression	Adult health centre attenders	Baseline and on randomly selected days at 6 and 12 months of implementation
Perceived social support	MSPSS	Perception of social support received	Individuals who receive HAP	3 and 6 months post-recruitment
	Bespoke tool			3 and 6 months post-recruitment
Treatment completion	Process data	Met treatment goals or completed the maximum number of sessions or were referred to mental health specialists	Individuals who receive HAP	Across the 12 months of implementation
Behavioural activation	PREMIUM Abbreviated Activation Scale	Patient-report activation levels	Individuals who receive HAP	3 and 6 months post-recruitment

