### Objectives {7}

Through the IMPRESS (*IMP*lementation of evidence based facility and community interventions to reduce the treatment gap for dep*RESS*ion) programme, we aim to increase both the contact coverage and effective coverage of a scaled-up, evidence-based psychosocial treatment for depression (Healthy Activity Program-HAP) [9] and, in doing so, reduce the treatment gap for depression in a cost-effective manner. We will do this by examining if the addition of a community intervention (Community Model) delivered by community volunteers enhances the population-level impact of scaled-up HAP in routine primary care (Facility Model) by increasing demand for HAP and improving HAP adherence and effectiveness. We will conduct an economic evaluation, to estimate the cost-effectiveness of the Community Model in comparison to the Facility Model, and use the estimates of the cost of the delivery of the interventions to model the financial sustainability of scaling it up across India.

Our
*primary hypotheses* are that the Community Model will be superior to the Facility Model in reducing the treatment gap for depression through

(1a) Increasing the demand for depression treatment in primary care (contact coverage outcome); and(1b) Reducing depressive symptoms at three months post-recruitment amongst those who screen positive for moderately severe and severe depression (effectiveness outcome)

(2)Our *secondary hypotheses* are that the Community Model will be superior to the Facility Model in

(2a) Achieving a sustained reduction in symptoms of depression;(2b) Increasing short-term and sustained remission from depression;(2c) Achieving a greater response to HAP;(2d) Increasing perceived social support;(2e) Achieving higher treatment completion rates; and(2f) Increasing patient-reported activation levels.

In addition, we also hypothesize that the Community Model will increase community awareness about depression.

(3)Finally, we hypothesise that the superior outcomes of the Community Model will be mediated through:

(3a) Increased community awareness about depression (for contact coverage);(3b) Greater perceived social support (for effective coverage);(3c) Higher treatment completion rates (for effective coverage); and(3d) Increased patient-reported activation levels (for effective coverage).

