### Study setting {9}

IMPRESS will be implemented in the state of Goa, west India. The population of Goa is just over 1.6 million people, with relatively high literacy rates (89% women, 95% men) compared with the national average (65% women, 82% men). We will conduct our trial in 28 clusters of villages associated with health centres in the public sector—20 primary health centres (PHCs), six community health centres (CHCs), and two sub-district hospitals (SDHs). These are frontline healthcare facilities forming the foundation of the public health system in Goa and are collectively referred to as health centres in the rest of this protocol. A typical PHC provides outpatient medical services and some inpatient/observation beds. CHCs perform similar roles to PHCs but cover a larger population and provide some specialist services. SDHs form an important link between PHCs/CHCs on one end and district hospitals on the other end. In addition to primary care, SDHs also provide some specialist services. Specialist mental healthcare (through a psychiatrist, psychologist, psychiatric social worker) is provided in some health centres through fortnightly or monthly clinics by the DMHP [12].

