### Criteria for discontinuing or modifying allocated interventions {11b}

We will discontinue treatment in participants who (a) report any serious adverse events (SAE) deemed possibly caused by the trial interventions and (b) refuse treatment after consenting. Such participants will receive a supported referral to the DMHP. Participants who develop serious suicidal ideation or risk of suicidal behaviour will receive supported referral to the DMHP to supplement the HAP. Additionally, participants who do not respond to the treatment at the end of eight sessions of HAP will also receive a referral to the DMHP. All these participants will be contacted for the outcome assessments, unless they withdraw their consent for follow-up.

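### Treatment completion accepts any specialist referral, so participants who start HAP and then refuse it, are discontinued, or stop after a supplementary referral can be scored as completers

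*Protocol article*

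**What the plan says.** Table 2 of the protocol article (Outcomes {12}) defines treatment completion by three alternatives joined by an or: "Met treatment goals or completed the maximum number of sessions or were referred to mental health specialists". The third has no qualifier on why or when the referral was made. The population in that row is "Individuals who receive HAP".

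The section on discontinuing or modifying interventions {11b} stops treatment in two groups: participants with an SAE judged possibly due to the interventions, and participants who refuse treatment once they have consented. It then states: "Such participants will receive a supported referral to the DMHP". For a third group it says: "Participants who develop serious suicidal ideation or risk of suicidal behaviour will receive supported referral to the DMHP to supplement the HAP". A fourth group, non-responders at the end of eight sessions, is also referred.

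Study setting {9} makes clear that the DMHP is a specialist service: "Specialist mental healthcare (through a psychiatrist, psychologist, psychiatric social worker) is provided in some health centres through fortnightly or monthly clinics by the DMHP".

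The post-trial care section {30} gives three alternative end states for people who receive HAP: treatment completed, dropped out, or referred to the DMHP. Objectives {7} uses completion twice, as secondary hypothesis 2e and as mediator 3c for the effectiveness outcome.

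**The concern.** One section requires a specialist referral when HAP is refused or discontinued, and the outcome table makes a specialist referral enough for completion. Taken together, refusing HAP after starting it becomes a way of completing it. The post-trial care section keeps apart the states that Table 2 merges, so the article does not hold one consistent meaning of completion.

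The community intervention is meant, among other things, to improve engagement with HAP and its completion. An outcome that can record refusal as completion does not measure that aim cleanly, and hypothesis 2e is tested on it. For mediator 3c, participants with little exposure to HAP join the completer group, which blurs the path from completion to PHQ-9. Referral is a case manager task (Table 1), and case managers are not blinded {17a}, so part of this outcome is set by staff who may know the arm.

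**Working it through.** The article states no completion, refusal or referral rate, so there is no figure to reproduce. The check has two parts.

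**1. What the referral alternative adds, route by route** (routes from {11b}, population from Table 2)

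- Refusal after starting HAP: referral required, HAP ended, inside the population. Newly counted as a completer.
- Discontinuation for an SAE possibly caused by the interventions: referral required, HAP ended. Newly counted, unless goals or maximum sessions were already reached.
- Suicide risk: referred while HAP continues. Counted from the moment of referral, and so misclassified if the participant later stops short of the other two criteria.
- Non-response at the end of eight sessions: referred, but already a completer through the maximum-sessions alternative. No effect.
- Refusal before any session: referral required, but probably outside the population, which is those who receive HAP.
- Silent non-attendance: no referral is stated. Not counted.

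Among the stated routes, the referral alternative therefore adds only refusers who had started, SAE discontinuations and mid-course supplementary referrals. The one route that looks like a planned end of HAP, non-response after eight sessions, does not need it.

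**2. Effect on the between-arm difference** (all rates assumed)

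Let c be the share who meet goals or complete the maximum sessions, and f the share of the remainder who are referred. Then

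recorded completion = c + f(1 − c).

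With the same f in both arms, the recorded difference is (1 − f) × (c_Community − c_Facility). Assume c = 60% in the Facility Model and 75% in the Community Model, a difference of 15 points:

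- f = 10%: 0.60 + 0.10 × 0.40 = 64.0%; 0.75 + 0.10 × 0.25 = 77.5%; difference 13.5 points.
- f = 25%: 0.60 + 0.25 × 0.40 = 70.0%; 0.75 + 0.25 × 0.25 = 81.25%; difference 11.25 points.
- f = 50%: 0.60 + 0.50 × 0.40 = 80.0%; 0.75 + 0.50 × 0.25 = 87.5%; difference 7.5 points.

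With unequal f, combining the values above:

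- Facility 25%, Community 10%: 77.5 − 70.0 = 7.5 points.
- Facility 50%, Community 10%: 77.5 − 80.0 = −2.5 points.
- Facility 10%, Community 25%: 81.25 − 64.0 = 17.25 points.

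The level of completion rises in each arm whenever f is above zero. The difference can be diluted, reversed or inflated.

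**The case against.** Much of the case on the other side stands, and it limits the point.

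- A reader might infer that drop-outs in general are scored as completers. The article does not support that. Patients who simply stop attending have no stated referral, and the post-trial care section lists drop-out apart from referral.
- Refusal after consenting naturally includes people who never start. They are probably outside the denominator, and Table 3 has a separate uptake indicator based on receiving at least one session.
- The SAE route covers only events possibly caused by the interventions. The harms section {22} does not expect SAEs from the trial, so this group is probably very small.
- Suicide-risk referral supplements HAP. Those patients are misclassified only if they later stop early.
- A reader might also infer that the Facility Model has more refusals, so that the rule must shrink the effect, perhaps by half. Nothing in the article gives refusals by arm. Home visits by *Sangathis* could turn silent lapses into recorded refusals with a referral, which would raise recorded completion in the Community Model. The halving follows only from assuming f = 50%.

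It can also be said that this is one condensed table cell. The full protocol, the pre-defined referral protocol mentioned under consent {26a} and the coding rules of the PEERS app are not shown, and counting a planned step-up in care as the end of HAP is a legitimate choice. That is fair as to intent. But the article does state a definition, that definition is unconditional, and it conflicts with {11b} and {30}. This is a rule that gives the wrong answer when followed, not a detail left for later.

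**Conclusion.** The point holds in limited form, and the definition is wrong as written. Applied literally, Table 2 scores as completers those who start HAP and then refuse or are discontinued, and those referred mid-course who then stop. It does not touch silent non-attenders or non-responders after eight sessions, and probably not those who refuse before any session.

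The size and direction of the bias are unknown, because the article gives no refusal or referral rates. The figures above show how the rule behaves under assumed rates and do not predict what this trial will see. The effect on mediation is not quantified. Neither primary outcome nor the sample size is affected. Because completion carries a secondary hypothesis and a mediation path, and correction is cheap, it should be corrected before analysis.

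**What to change.** Reconcile Table 2, {11b} and {30} by changing the outcome definition. A referral triggered by refusal or discontinuation, or made to supplement HAP while it continues, should not by itself count as completion. A referred participant should count only by meeting goals, by completing the maximum sessions, or through a referral recorded as a planned end of HAP. State how refusal and discontinuation are classified, and apply the same definition to the completer indicator in Table 3.

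This needs a reason-for-referral field in the process data; the PEERS app already records session data and tracks progress through treatment. The cost is one line in the definition, one extra data field and a somewhat lower reported completion rate. Referral practice itself is unchanged, and no view is taken on it here.

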#### Qualitative data

These will include data collected using in-depth interviews (IDIs) and focused group discussions (FGDs) with various stakeholders involved in delivering the interventions, individuals with depression, and decision makers and implementors at various levels in the health system as outlined in Table 3.

**Table 3 Tab3:** Implementation monitoring and evaluation

**Indicator**	**Source**	**When**	**RE-AIM Dimension**^a^
*Patient level*			
Number of HAP patients who were followed up in the community	Process data from *Sangathi* registers	During implementation	R
% eligible for HAP who receive at least one session of HAP (uptake)	Process data from screening register, PEERS app	During implementation	I
% treatment completers	Process data from PEERS app	During implementation	I
Adherence to homework	Process data from PEERS app	During implementation	I
Acceptability of community intervention	In-depth interviews (IDIs) with individuals receiving the intervention	After completion of 6-month outcome evaluation	R
Number of people with possible depression referred by *Sangathis*	Process data from *Sangathi* registers	During implementation	R
*Counsellor level*			
Characteristics of counsellors who agreed to join the programme	Process data from training register	During training	A
Knowledge	Multiple Choice Questionnaire administered to HAP counsellors	Pre- and post-training	I
Acceptability of training	Focused group discussions (FGD) with counsellors and HAP facilitators	Post-training	A
Fidelity of training	Direct observation of HAP facilitators	During training	I
Skill- based competency	ENACT tool to rate skills of HAP counsellors	Pre- and post-internship	I
Therapy quality	PEERS app	During implementation	I
Acceptability of supervision	IDIs/FGDs with counsellors and HAP facilitators	During implementation	A
Number/duration of supervision sessions attended (feasibility)	PEERS app	During implementation	I
Acceptability of HAP	IDIs/FGDs with counsellors	During implementation	A
Fidelity	Audio recording of HAP sessions	10% of audio-recordings by independent evaluators	I
Perceived benefits and barriers of implementing and sustaining programme	IDIs/FGDs with counsellors	During implementation	A
*Sangathi level*			
Characteristics of *Sangathis* who agreed to join the programme	Process data from recruitment register	During training	A
Acceptability of training	IDIs/FGDs with *Sangathis* and *Sangathi* facilitators	Post-training	A
Number of attempts to complete module knowledge tests	Process data from e-course	During training	I
Acceptability of supervision	IDIs/FGDs with *Sangathis* and *Sangathi* facilitators	During implementation	A
Number/duration of supervision sessions attended (feasibility)	Process data from facilitator log	During implementation	A
Acceptability of community intervention	IDI/FGDs with *Sangathis*	During implementation	A
Retention	Process data	During implementation	A
Type and number of community activities conducted	Process data from facilitator log	During implementation	I
Number of people attending community activities	Process data from facilitator log	During implementation	R
Number of *Sangathi* contacts with participants in the effectiveness coverage sample	Process data from facilitator log	During implementation	I
Perceived benefits and barriers of implementing and sustaining programme	IDI/FGDs with *Sangathis*	During implementation	A
Costs borne towards the delivery of the community intervention	Form for collecting costs borne by *Sangathis* and the community	During implementation	E
*Health systems level*			
Perceived benefits and barriers of implementing and sustaining programme	IDI/FGD with health department officials	At the end of implementation	A
Fiscal capacity to cover the costs of scale-up by the government	Macro-level data collection tool	During implementation	I
Readiness to change	ORIC administered to health department officials and other staff from the health centres, e.g. counsellors, and health officers	Baseline and 12 months	A

^a^*R* Reach, *E* Effectiveness, *A* Adoption, *I* Implementation, *M* Maintenance

#### Process indicators, implementation monitoring, and evaluation (Table 3)

These data, informed by the RE-AIM framework, will be collected at the level of the patient, counsellor, *Sangathi*, and health-system. These include data collected routinely as a part of the implementation (e.g. treatment completion rates), qualitative data, and administration of standardised tools. At the level of the patients who receive HAP, we will collect data about treatment initiation (uptake), follow-up rate in the community, homework adherence rate, treatment completion rate, referral from the community, and overall acceptability of the community intervention. At the level of the counsellors, we will collect data related to the characteristics of counsellors, knowledge acquisition through the training, acceptability of training, fidelity of training delivered, acquisition of skill-based competency, quality of therapy delivered, feasibility and acceptability of supervision, acceptability of HAP, fidelity of the HAP delivered, and perceived benefits and barriers of implementing and sustaining the program. At the level of the *Sangathi,* we will collect data related to characteristics of *Sangathis*, acceptability of training, number of attempts to complete module-based questions, feasibility and acceptability of supervision, acceptability of community intervention, retention in the program, type and number of community activities conducted, number of people attending community activities, number of *Sangathi* contacts with patients, and perceived benefits and barriers of implementing and sustaining the program. Finally, at the level of the health system, we will collect data from various stakeholders (e.g. health department officials) about perceived benefits and barriers of implementing and sustaining the program, the fiscal capacity to cover the costs of scale-up by the government, and readiness to change using the Organizational Readiness for Implementing Change (ORIC) tool. The ORIC has nine items that measure organisational readiness to change in two domains, change commitment and change efficacy [28].

